| Rationale: Clarification of treatment guidelines in case of specific PegIFN-related AEs to make it clear that RBV monotherapy is not allowed.                                                                                                                                                                                                     |                                                                                                                                                                                                                 |
| 9.5.7.6.1
Neuropsychiatric
Symptoms;
9.5.7.6.5 Decreased
WBC
9.5.7.6.5 Decreased
platelets                                                                                                                                                                                                                                             | Stated explicitly that if PegIFN $\alpha$ -2a has to be discontinued for management of the AE, then TMC435 and RBV must also be discontinued                                                                    |

| Applicable Section(s)                                                                                                                                              | Description of Change(s)                                                                                                |
|--------------------------------------------------------------------------------------------------------------------------------------------------------------------|-------------------------------------------------------------------------------------------------------------------------|
| Rationale: Correction of an error: both male and female subjects must discontinue study medication if they fail to comply with contraception requirements   |                                                                                                                         |
| 1.3.5 Overall benefit/risk assessment                                                                                                                              | Deletion of erroneous text                                                                                              |

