##### **Reproductive Risks and Pregnancy:**

No studies with TMC435 were performed in pregnant women. In animal studies, TMC435 had no effect on fertility and early embryonic and fetal development in rats up to doses of 500 mg/kg corresponding to an exposure of 221 µg.h/mL in plasma. No human data on the effect of TMC435 on fertility are available. Therefore, pregnancy and breastfeeding have been exclusion criteria for all clinical studies with TMC435 conducted to date. Women of childbearing potential and men included in studies with TMC435 have been required to use effective methods of birth control.

Significant teratogenic and/or embryocidal effects have been demonstrated in animals exposed to RBV. Ribavirin may persist in non-plasma compartments for as long as 6 months. Ribavirin is contraindicated in females who are pregnant or breastfeeding and in male partners of females who are pregnant. Ribavirin should not be started unless a report of a negative pregnancy test has been obtained immediately prior to initiation of therapy. In addition, extreme care must be taken to avoid pregnancy in females of childbearing potential or males having a female partner of childbearing potential taking RBV for at least 6 months after completion of PegIFNα-2a and RBV therapy (or longer, if dictated by local regulations). Subjects must consent to utilize 2 effective methods of birth control (as specified in Section 4.3), and male adolescents should not donate sperm while participating in this study and for at least 6 months after receiving the last dose of RBV (or longer, if dictated by local regulations; see Section 4.3 for more detail).

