### **1.5.5. Overall Benefit/Risk Assessment**

Based on the available data and proposed safety measures, the overall risk/benefit assessment for this clinical study is acceptable for the following reasons:

- Safety data from Phase 1, 2, and 3 studies showed that TMC435 was generally safe and well tolerated in healthy and HCV-infected adults at all doses tested, including the 150 mg once daily dose that is currently used in the ongoing Phase 3 studies.
- Only subjects who meet all of the inclusion criteria and none of the exclusion criteria (as specified in the protocol) will be allowed to participate in this study. The selection criteria

include adequate provisions to minimize the risk and protect the well-being of subjects in the study.

- Safety will be closely monitored by the investigator throughout the study. Safety and tolerability assessments (including vital signs, physical examination, and clinical laboratory tests) will be performed at scheduled visits throughout the study. Adverse events will be monitored from signing of the informed consent onwards until 4 weeks after last study medication intake. Thereafter, only AEs considered related to TMC435 will be reported. SAEs will be reported until 30 days after last study-related procedure.
- Several safety measures have been proposed to minimize potential risk to subjects, including:
  - The safety monitoring and toxicity management plan in this study (see Section 9.5.7) takes into account the known toxicities of the PI class, the safety and tolerability profile of TMC435 as determined in studies in healthy subjects and in (ongoing) studies in HCV-infected subjects, the findings in nonclinical studies, and the safety and tolerability profile of PegIFN $\alpha$ -2a and RBV.
  - Subjects must discontinue all study medication (TMC435, PegIFN $\alpha$ -2a and RBV) for any of the following reasons:
    - withdrawal of consent.
    - The subject meets a virologic stopping criterion at Week 4 or 12 or experiences viral breakthrough at any time point during treatment (see Section 6.3).
    - The investigator believes that for safety reasons (e.g., AE) it is in the best interest of the subject to discontinue study treatment.
    - The subject becomes pregnant.
    - The subject fails to comply with the contraception requirements (refer to Section 4.3).
    - The subject experiences a grade 3 or 4 rash/allergic reaction (see Sections 9.5.7.1 and 9.5.7.2).

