### **4.3. Prohibitions and Restrictions**

Potential subjects must be willing and able to adhere to the following prohibitions and restrictions during the course of the study to be eligible for participation.

Significant teratogenic and/or embryocidal effects have been shown in animals exposed to RBV. Ribavirin may persist in non-plasma compartments for as long as 6 months. It is contraindicated in women who are pregnant or breastfeeding and in male partners of women who are pregnant. In addition, extreme care must be taken to avoid pregnancy in female subjects and in female partners of male subjects taking RBV for at least 6 months after completion of PegIFN $\alpha$ -2a/RBV therapy (or longer, if dictated by local regulations). Ribavirin should not be started unless a report of a negative pregnancy test is obtained immediately prior to initiation of therapy. Therefore, the following precautions must be adhered to:

1. A woman of childbearing potential who is heterosexually active must remain on two different highly effective methods of birth control (see inclusion criteria in Section 4.1) from screening and up to 6 months after the last dose of RBV (or longer if dictated by local regulations).
2. A woman using oral contraceptives must use an additional birth control method (see inclusion criterion in Section 4.1).
3. A man who is sexually active with a woman of childbearing potential and has not had a vasectomy must agree to use two different highly effective methods of birth control (including at least one barrier method). A man who is sexually active with a woman of childbearing potential and has had a vasectomy must agree to use a barrier method of birth control e.g., either condom with spermicidal foam/gel/film/cream/suppository or partner with occlusive cap (diaphragm or cervical/vault caps) with spermicidal foam/gel/film/cream/suppository. All men must also not donate sperm during the study and for 6 months (or longer if dictated by local regulations) after the last dose of RBV.

For male subjects, it is the responsibility of the subject to ensure that his partner (or partners) is (are) not pregnant prior to entry into the study or becomes pregnant during the treatment and post-therapy follow-up phase of the study. During treatment with RBV, female partners of male participants should follow the guidelines as outlined in the manufacturer's prescribing information for RBV.

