Dose adjustments of TMC435 are not allowed. **If TMC435 is discontinued because a subject meets a virologic stopping rule, it must not be restarted.** If PegIFN $\alpha$ -2a is discontinued for tolerability or toxicity issues or if > 2 consecutive weekly injections are missed, RBV and TMC435 must be discontinued. If RBV is interrupted for more than 14 consecutive days, TMC435 must be discontinued; PegIFN $\alpha$ -2a may be continued at the investigator's discretion. Any additional interruption of RBV or PegIFN $\alpha$ -2a should be discussed with the sponsor on a case-by-case basis.

Temporary interruption of TMC435 during the treatment period will be allowed in the event of suspected toxicity, as long as the temporary interruption is associated with and can be linked to an AE or SAE (permanent discontinuation of one or more study medications may be required, see Section 9.5.7 and Section 10.2). One single treatment interruption for toxicity reasons of TMC435 will be allowed with a maximum duration of 4 days. Treatment with TMC435 should be reinstituted as soon as the AE is stabilized. Reinstitution of TMC435 treatment after interruption for longer than 4 days or after repeated interruption is generally disallowed unless approval by the sponsor has been obtained after discussion on a case-to-case basis.

All modifications, interruptions, or discontinuations of TMC435, PegIFN $\alpha$ -2a, and RBV will be recorded in the eCRF.

Study-site personnel will instruct subjects on how to store study drug for at-home use as indicated for this protocol.

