### **10.2. Discontinuation of Study Treatment**

If a subject's study treatment must be discontinued before the end of the treatment regimen, this will not result in automatic withdrawal of the subject from the study.

At the discretion of the investigator, all study medication (TMC435, PegIFN $\alpha$ -2a and RBV) may be discontinued for any of the following reasons:

- An SAE occurs.
- The subject fails to comply with the protocol or study staff requirements.

All study medication (TMC435, PegIFN $\alpha$ -2a and RBV) must be discontinued for any of the following reasons:

- withdrawal of consent.
- The subject meets a virologic stopping criterion at Week 4 or 12 or experiences viral breakthrough at any time point during treatment (see Section 6.3).
- The investigator believes that for safety reasons (e.g., AE) it is in the best interest of the subject to discontinue study treatment.
- The subject becomes pregnant.
- A subject fails to comply with the contraception requirements (in female subjects; refer to Section 4.3).
- The subject experiences a grade 3 or 4 rash/allergic reaction (see Sections 9.5.7.1 and 9.5.7.2).
- The subject experiences severe worsening of hepatic disease (see Section 9.5.7.4).

Subjects must discontinue investigational medication (TMC435) and may continue PegIFN $\alpha$ -2a and/or RBV alone if:

- They require treatment with one of the medications included in the list of disallowed concomitant medications (see Section 8).

- The subject experiences grade 4 ALT/AST elevations  $> 2 \times$  baseline value and concurrent grade 4 bilirubin values and the ALT/AST and bilirubin values continue to meet grade 4 criteria at re-testing performed 72 hours after receipt of the results (see Section 9.5.7.3).
- The subject experiences a grade 3 or 4 AE (other than the rash/allergic reaction AE mentioned above) or confirmed grade 3 or 4 laboratory abnormality (other than grade 3 isolated increases in AST/ALT or bilirubin) considered to be at least possibly related to TMC435 (2 consecutive measurements no more than 72 hours after receipt of first results). This excludes AEs or laboratory abnormalities that are not considered to be at least possibly related to TMC435. Subjects who have known Gilbert's disease and experience isolated grade 4 elevated indirect bilirubin can continue the investigational medication at the investigator's discretion.

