### **12.3.3. Pregnancy**

All initial reports of pregnancy must be reported to the sponsor by the study-site personnel within 24 hours of their knowledge of the event using the appropriate pregnancy notification form. Abnormal pregnancy outcomes (e.g., spontaneous abortion, stillbirth, and congenital anomaly) are considered SAEs and must be reported using the Serious Adverse Event Form. Any subject who becomes pregnant during the study must discontinue further study treatment.

In case the partner of a male subject becomes pregnant, the male subject must abstain from sex with that female partner during the pregnancy. It is highly recommended that pregnancies in partners of male subjects included in the study are reported by the investigational staff within 24 hours of their knowledge of the event using the appropriate pregnancy notification form. In view of the privacy regulations, a separate consent of the partner will be obtained at that time.

Follow-up information regarding the outcome of the pregnancy and any postnatal sequelae in the infant will be required.

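### Section 10.2 limits to women a mandatory stop of all study medication for contraception non-compliance that Section 1.5.5 applies to every subject

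*Protocol*

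**What the plan says.** Section 1.5.5 (Overall Benefit/Risk Assessment) presents a list of mandatory reasons to stop TMC435, PegIFNα-2a and RBV as one of the safety measures behind its statement that the benefit/risk is acceptable. One item reads "The subject fails to comply with the contraception requirements (refer to Section 4.3". It carries no limit by sex.

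Section 10.2 (Discontinuation of Study Treatment) gives the corresponding mandatory list. There the item reads "A subject fails to comply with the contraception requirements (in female subjects; refer to Section 4.3". A separate list in the same section names reasons for which the investigator may, but need not, stop all drugs. One of these is "The subject fails to comply with the protocol or study staff requirements".

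Section 4.3, to which both mandatory items refer, binds men as well as women. Its item 3 concerns men whose female partner could conceive, and says that one who "has not had a vasectomy must agree to use two different highly effective methods of birth control". A vasectomized man with such a partner must use a barrier method.

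The Protocol Amendments section, in the entries for Amendment INT-1, records the correction of an error with the rationale that "both male and female subjects must discontinue study medication if they fail to comply with contraception requirements". The only place listed for that correction is the overall benefit/risk assessment, numbered 1.3.5 at the time.

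**The concern.** The two sections state the same stopping rule with different scope. For a woman who fails the contraception requirements they agree. For a man, one section makes the stop compulsory and the other does not.

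The rule protects against fetal exposure to RBV, which the protocol describes as having significant teratogenic and/or embryocidal effects in animals. Section 1.5.5 relies on the compulsory stop, for any subject, when it argues that the risk is acceptable. The section whose subject is treatment discontinuation does not deliver that measure for men. A site that reads only Section 10.2 could keep a non-compliant man on treatment and believe it was following the protocol.

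**Working it through.** No arithmetic applies. The check is a comparison of current text.

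**Step 1. Compare the mandatory all-drug lists.**

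| Reason | Section 1.5.5 | Section 10.2 |
|---|---|---|
| Withdrawal of consent | yes | yes |
| Virologic stopping criterion or viral breakthrough | yes | yes |
| Investigator's view that stopping is in the subject's interest for safety | yes | yes |
| Subject becomes pregnant | yes | yes |
| Failure of the contraception requirements | any subject | female subjects only |
| Grade 3 or 4 rash or allergic reaction | yes | yes |
| Severe worsening of hepatic disease | yes | yes |

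There are seven items in each list. Six agree and one differs.

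**Step 2. Does the difference have content?** It would be empty if Section 4.3 placed no duty on men. Item 3 does place one, so a man can fail the requirements and the two lists then give different answers.

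**Step 3. What does Section 10.2 leave for a non-compliant man?** He is outside the mandatory contraception item. Two other items could reach him:

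- The item on failing to comply with the protocol is in the discretionary list, so the investigator may stop treatment but is not required to.
- The mandatory safety item is triggered by the investigator's own belief about what is best for the subject. The hazard here falls on a partner's pregnancy rather than on the man.

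Both routes depend on judgement. That men are left to judgement is an inference from the structure of Section 10.2, which does not say so in words.

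**Step 4. Which section is right?** Both sentences are current body text, so this is not a difference between an amendment log and the text that replaced it. The INT-1 rationale is used only as evidence of intent. It says that both sexes must discontinue, which is the rule in Section 1.5.5.

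**The case against.** The best case on the other side is that the conflict is narrow. Section 10.2 does not say that a non-compliant man may continue, and a site that stops him satisfies both sections. That is true, and it limits the size of the point. It does not remove the conflict, because a stop that is compulsory in one section and optional in the other is still two different rules.

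A reader might infer that the protocol actively sends sites to Section 10.2 for this event. The cross-references do not show that. The pointer in Section 6.2, "permanent discontinuation of one or more study medications may be required, see Section 9.5.7 and Section 10.2", concerns interruption of TMC435 for suspected toxicity. The references to Section 10.2 in the toxicity tables concern allergic reaction, ALT/AST, bilirubin and psychiatric symptoms. Neither Section 4.3 nor Section 12.3.3 points to Section 10.2. What remains is that, by its title, Section 10.2 is the natural place to look.

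A reader might also infer from the amendment entry that Section 10.2 carried the same restriction before INT-1 and was overlooked. That is plausible, but no earlier version of Section 10.2 is in the document. The point does not need it.

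**Conclusion.** The item in Section 10.2 is wrong as written. It is an internal inconsistency in a safety stopping rule, and it is minor in size: one of seven items, and men only. The primary test, its alpha and power, and all estimates are untouched. The protocol gives no sex mix, partner share or contraception failure rate, so the number of men affected cannot be derived. The expected split between 12 and 24 weeks of treatment describes all subjects and would not supply that number. The conclusion assumes that the INT-1 rationale states the sponsor's intent.

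A stronger reading is that the protocol also leaves a gap when a male subject's partner becomes pregnant. In that event Section 12.3.3 says "In case the partner of a male subject becomes pregnant, the male subject must abstain from sex with that female partner during the pregnancy", and it adds recommended reporting and outcome follow-up but names no drug action. The document does not support calling this an error. Section 1.5.4 states "Ribavirin is contraindicated in females who are pregnant or breastfeeding and in male partners of females who are pregnant", Section 4.3 repeats the contraindication, and Copegus is given according to its prescribing information. Section 6.2 already says what follows if RBV is interrupted for more than 14 consecutive days: TMC435 must stop, and PegIFNα-2a may continue at the investigator's discretion. Where the partner-pregnancy instruction stands is a matter of placement, and an all-drug stop for that event would be new policy.

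**What to change.** In the mandatory list of Section 10.2, delete the three words restricting the contraception item to female subjects, with the semicolon that follows them. The parenthesis then holds only the reference to Section 4.3, and the item has the same scope as in Section 1.5.5. Leave Section 1.5.5, Section 4.3 and the discretionary list as they are.

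The cost is a three-word deletion in the next amendment. It adds no visit or test, and Section 1.5.5 already states the rule. The practical effect is that a man who fails the contraception requirements stops all three drugs by rule rather than by judgement.

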**Table 2: Guidelines for Subjects Developing Allergic Reactions**

| WHO Toxicity Grade | Definitions                                              | Investigator Action                                                                                                                                                                                                                                                          |
|--------------------|----------------------------------------------------------|------------------------------------------------------------------------------------------------------------------------------------------------------------------------------------------------------------------------------------------------------------------------------|
| Grade 1            | Pruritus suggestive of an allergic reaction without rash | May continue investigational medication (TMC435) or have their investigational medication (TMC435) discontinued at the investigator's discretion.
May continue treatment with PegIFN $\alpha$ -2a or RBV at the investigator's discretion.                                |
| Grade 2            | Localized urticaria                                      | May continue investigational medication (TMC435) or have their investigational medication (TMC435) discontinued at the investigator's discretion.
Rechallenge is not allowed.
May continue treatment with PegIFN $\alpha$ -2a or RBV at the investigator's discretion. |
| Grade 3            | Generalized urticaria, or Angioedema                     | Permanently discontinue study medication (TMC435, PegIFN $\alpha$ -2a and RBV) (see Section 10.2).                                                                                                                                                                           |
| Grade 4            | Anaphylaxis                                              | Permanently discontinue study medication (TMC435, PegIFN $\alpha$ -2a and RBV) (see Section 10.2).                                                                                                                                                                           |

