**Table 4: Treatment-emergent Grade 4 ALT or AST elevation or Grade 4 total bilirubin elevation**

| WHO Toxicity Grade | AST or ALT, Ranges | Total Bilirubin, Ranges |
|--------------------|--------------------|-------------------------|
| Grade 4            | > 10.0 x ULN       | > 5.0 x ULN             |

If the grade 4 ALT/AST value is > 2 x baseline value, a confirmatory measurement should be performed within 72 hours after receipt of the results. In case of a confirmed value, the investigational medication should be discontinued.

For isolated grade 4 bilirubin values, subjects should have a confirmatory measurement within 72 hours after receipt of the results. In case of a confirmed grade 4 value, the investigational medication should be discontinued. Treatment with PegIFN $\alpha$ -2a and RBV may be continued at the investigator’s discretion if the increased values are not accompanied by signs of liver decompensation. Subjects who have known Gilbert’s disease and experience isolated grade 4 elevated indirect bilirubin can continue the investigational medication at the investigator’s discretion.

For concurrent grade 4 ALT/AST elevations > 2 x baseline value and grade 4 bilirubin values, subjects should have a confirmatory measurement within 72 hours after receipt of the results. In case of confirmed grade 4 elevations, the investigational medication should be discontinued. Treatment with PegIFN $\alpha$ -2a and RBV may be continued at the investigator’s discretion if the increased values are not accompanied by signs of liver decompensation.

Subjects should be followed until return to predose baseline or stabilization of ALT/AST and/or bilirubin elevation.

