| Moderate              | May continue study medication or have their study medication discontinued at the investigator's discretion.
When study medication is continued, reduce to PegIFN $\alpha$ -2a dose to 135 $\mu$ g (in some cases, a second dose reduction to 90 $\mu$ g may be needed).
Evaluate once weekly (office visit at least every other week). | Consider psychiatric consultation.

Continue reduced dosing. | If symptoms improve and are stable for 4 weeks, may resume normal visit schedule.
Continue reduced dosing or return to normal dose. | See grade 3 symptoms             |
| Severe                | Permanently discontinue PegIFN $\alpha$ -2a b (see Section 10.2).
Obtain immediate psychiatric consultation.                                                                                                                                                                                                                   | Psychiatric therapy necessary.                                     |                                                                                                                                        |                                  |

a Refer to the Diagnostic and Statistical Manual of Mental Disorders – fifth edition (DSM-V) for definitions.

b In case PegIFN $\alpha$ -2a has to be discontinued, TMC435 and RBV must be discontinued as well.

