**Table 10: Guidelines for Subjects Developing Decreased Platelet Count**

| Laboratory values                            | PegIFN $\alpha$ -2a dose | Discontinue PegIFN $\alpha$ -2a a if |
|----------------------------------------------|--------------------------|-------------------------------------------------|
| Platelet count $\geq$ 50,000/mm  | Maintain 180 $\mu$ g     | Platelet count < 25,000/mm          |
| Platelet count < 50,000/mm       | Reduce to 90 $\mu$ g     |                                                 |

a In case PegIFN $\alpha$ -2a has to be discontinued, TMC435 and RBV must be discontinued as well.

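### Sections 1.5.5, 9.5.7.2 and 10.2, read literally, allow ribavirin to continue without peginterferon, which Section 6.2 and the footnotes to Tables 7, 9 and 10 rule out

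*Protocol*

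**What the plan says.** On the permissive side, Section 10.2 lists events that require TMC435 to stop: need for a disallowed drug, confirmed concurrent grade 4 transaminase and bilirubin elevations, and grade 3 or 4 events or confirmed laboratory abnormalities at least possibly related to TMC435. The list opens with "Subjects must discontinue investigational medication (TMC435) and may continue PegIFN $\alpha$ -2a and/or RBV alone if". Section 1.5.5 opens its matching list in the same way. For grade 1 and grade 2 allergic reactions, Table 2 says "May continue treatment with PegIFN $\alpha$ -2a or RBV at the investigator's discretion", and the Section 9.5.7.2 text for both grades agrees.

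On the restrictive side, Section 6.2 says that if PegIFN is "discontinued for tolerability or toxicity issues or if > 2 consecutive weekly injections are missed, RBV and TMC435 must be discontinued". The footnotes to Tables 7 (psychiatric symptoms), 9 (white cells) and 10 (platelets) all carry the sentence "In case PegIFN $\alpha$ -2a has to be discontinued, TMC435 and RBV must be discontinued as well".

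Section 6.2 also allows an interruption of up to 2 consecutive PegIFN injections, so a short gap does not by itself force RBV to stop.

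**The concern.** Once TMC435 is stopped, three regimens remain: PegIFN with RBV, PegIFN without RBV, and RBV without PegIFN. The protocol treats the first two consistently. The third is open under one set of sections and closed under another, and no order of precedence is stated.

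These are instructions on what a subject takes after a serious toxicity, so two sites could act differently on the same laboratory result. There are consequences for the data too. The Part 4 schedule, with its early withdrawal visit and its visit 4 weeks later, applies only when all study medication has been stopped. A subject kept on RBV would stay on the regular schedule. Viral breakthrough is defined as occurring on study treatment, whereas relapse requires undetectable HCV RNA at actual end of treatment followed by a return during follow-up. The label given to a viral return could therefore depend on which section the site followed.

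**Working it through.** No arithmetic applies. The check sets the current texts side by side.

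1. **PegIFN with RBV.** Allowed by Sections 1.5.5 and 10.2. Section 9.5.7.3 agrees, and it is the section that the liver item in 10.2 refers to: "Treatment with PegIFN $\alpha$ -2a and RBV may be continued at the" investigator's discretion. No conflict.

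2. **PegIFN without RBV.** Allowed by Sections 1.5.5 and 10.2. Section 6.2 (RBV interrupted for more than 14 consecutive days) and Table 8 footnote b also leave PegIFN to the investigator's discretion. No conflict.

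3. **RBV without PegIFN.** Allowed by the *or* in Sections 1.5.5, 9.5.7.2 and 10.2 and in Table 2. Not allowed by Section 6.2 when PegIFN is discontinued for tolerability or toxicity. The missed-injection limb of 6.2 names no reason: with weekly dosing, the third consecutive missed injection falls three weeks after the last one given, so a lasting PegIFN stop for any cause is caught. The footnotes to Tables 7, 9 and 10 say the same for their toxicities. Conflict.

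4. **One event under both rules.** Take a confirmed platelet count below 25,000/mm³ judged possibly related to TMC435.
   - Attachment 2 puts 20,000 to 49,000/mm³ in grade 3 and anything below 20,000/mm³ in grade 4, so the value is at least grade 3.
   - Section 9.5.7.6 notes that the events it covers may also be due to TMC435. Section 9.5.7.5 excludes only the toxicities in 9.5.7.1 to 9.5.7.4, so platelets remain within it.
   - Under 10.2, TMC435 stops and RBV alone is among the permitted continuations.
   - Under Table 10, PegIFN stops, and once it "has to be discontinued, TMC435 and RBV must be discontinued as well".
   - The two routes give different answers for RBV.

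5. **Cross-references.** Table 7 tells the site to stop PegIFN for severe symptoms and points to 10.2. Section 6.2 also points to 10.2. Section 10.2 does not point to 6.2 and contains no rule tying RBV to PegIFN. A reader who follows the references arrives at the permissive text.

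6. **Effect on SVR12.** SVR12 needs undetectable HCV RNA at actual end of treatment and again 12 weeks after *planned* end of treatment. The planned date does not move with the drug choice. A subject with a lasting viral return is detectable at the planned time point under either reading and fails SVR12 both ways.

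7. **Effect on the secondary label and follow-up.** If a viral return on RBV alone counts as occurring on study treatment, it may be called breakthrough. The same return after all drugs have stopped may be called relapse. Part 4, footnote a, follows breakthrough discontinuations for only 4 weeks after withdrawal and the other groups it lists to Week 36 or Week 48. The protocol does not say whether RBV alone counts as study treatment here, so this effect is possible but not established.

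**The case against.** The strongest reply is that a general permission yields to a specific requirement: 10.2 says what may continue, and 6.2 then limits it. The triggers in 10.2 do not in themselves call for stopping PegIFN, two of the three continuations covered by its wording are sound, and elsewhere the protocol uses *alone* to mean without TMC435. The introduction to Section 9.5.7 also sends the reader to Section 6.

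Part of this stands. The conflict is confined to one combination, and a PegIFN interruption of up to 2 injections with RBV continuing is compatible with 6.2. It would therefore be too broad to say that RBV must stop whenever PegIFN stops. But the reply does not remove the conflict. The reference in 9.5.7 to Section 6 concerns discontinuing TMC435 only, 10.2 gives no pointer to 6.2, and the platelet example falls under both rules. Where the protocol means both companion drugs together, as in 9.5.7.3, it says so.

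A reader might also try to size the problem from Section 1.2, which reports TMC435 or placebo stopped for adverse events in 1.8% of TMC435-treated subjects, and pruritus (grouped term) in 22.0%. Neither rate measures it. The first is stated without regard to PegIFN and RBV. The second is not limited to pruritus suggesting an allergic reaction without rash, and such subjects may simply continue all drugs. Only subjects who stop PegIFN and keep RBV are affected, and the documents give no figure for them.

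The log entry for Amendment INT-1 touches on RBV monotherapy, but it describes past changes and the point does not depend on it.

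**Conclusion.** The inconsistency is real, lies in the current text and concerns one combination: RBV continued after a PegIFN discontinuation that triggers Section 6.2 or a footnote to Table 7, 9 or 10. Its importance is that conflicting instructions bear on subject safety. It also determines whether Part 4 applies, and it may alter the breakthrough or relapse label in a small number of subjects whose count cannot be estimated from the documents.

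A reader might infer that the primary result is at risk. The documents do not support this: a lasting viral return fails SVR12 under either reading, and no material effect on the SVR12 conclusion, sample size, power or alpha is shown. Nor is it an error that the protocol leaves the dating of actual end of treatment open, since that derivation commonly belongs in the SAP.

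The conclusion rests on a literal reading of *and/or* and *or*, and on the absence of any stated precedence. It takes no position on which clinical rule is right.

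**What to change.** Reconcile Section 1.5.5, the grade 1 and grade 2 text of Section 9.5.7.2, the grade 1 and grade 2 rows of Table 2, and Section 10.2 with Section 6.2 and the footnotes to Tables 7, 9 and 10. One statement, with its content chosen by the sponsor, should say which remaining drugs may continue once TMC435 is stopped and which may continue once PegIFN is stopped, and how that relates to the permitted short interruptions. Use the same words in every place, and add a cross-reference between 10.2 and 6.2.

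The cost is wording in the next amendment. It needs no additional subjects, visits or assessments and no change to the planned analyses.
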